## **1. STUDY OBJECTIVES**

### **1.1 Primary Objective**

**Aim 1.** Explore the predictive relationship and the association between *ascending sensitization* measures and clinical response to acupuncture.

*Hypothesis 1: augmented temporal summation (TS), and more wide-spread pain (WSP) (quantified by number of painful areas marked by the participant on a standardized body map) will be associated with greater pain reduction in the verum arm than in the placebo arm; decreased pressure pain threshold (PPTr) will be associated with greater pain reduction in the placebo arm than the verum arm.*

*Aim 2. Explore the predictive relationship and the association between **descending modulatory** measures and clinical response to acupuncture.*

*Hypothesis 2: decreased conditioned pain modulation (CPM), and more favorable psychological state, measured by less pain catastrophizing, better self-efficacy in coping and in pain management, will be associated with greater pain reduction in the verum than the placebo arm; expectation of positive treatment outcome will be associated with pain reduction in both the verum and the placebo arm.*

*Aim 3. **Exploratory model building** to predict pain reduction by electroacupuncture.*

*Hypothesis 3. A mathematical model relating key baseline characteristics to percent pain reduction will be developed using advanced techniques, and this model will be tested using cross-validation within the proposed pilot.*

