## 715 5.1.2 Details of VA Administration

### 716 A. Rationale and Treatment Modules

717 The VA treatment protocol aims to treat low back pain with both local (anatomy driven) and distal  
718 (energetic, meridian driven) approaches. It has two principal modules (1 local, 1 distal) and two optional  
719 modules (also 1 local, 1 distal).

720 The principal modules consist of Module #1 and #2, as shown below in Figure 5 and Figure 6,  
721 respectively. Both are activated in ALL treatment sessions. Module #1 represents the local approach. It is  
722 a modified PENS (percutaneous electrical nerve stimulation), where key Bladder back Shu points in the  
723 affected dermatomes are needled and electrically stimulated (see “Ghonaie EA, Craig WF, White PF, et  
724 al. *JAMA* 1999; 281(9): 818-23” for details of the original protocol). Module #2, the distal approach,  
725 aims to tonify Shaoyin-Taiyang meridians by needling the following points: KI-3, KI-7, HR-3, SI-3, BL-40.  
726 Out of these, KI-3 (negative) and KI-7 (positive) are electrically stimulated as a pair. Two additional  
727 points, GV-3 and GV-20 will be needled to tonify Governor’s Vessel meridian.

[figure not shown]

Figure 5 - Module 1: Modified PENS (obligatory)

[figure not shown]

Figure 6 - Module 3: Periosteal (optional)

728

[figure not shown]

Figure 7 - Module 2: Principle Meridians (Obligatory)

[figure not shown]

Figure 8 - Module 4: Distinct Meridian Activation (optional)

729 The optional modules are #3 (local) and #4 (distal). First, at baseline, if the back pain radiates to the  
 730 buttocks and hips, we will activate module #3, the periosteal protocol for all session. It involves needling  
 731 and paired stimulation of the posterior superior iliac spine (PSIS) and a deep muscular point in the  
 732 affected gluteal region. The posterior superior iliac spine is identified by palpating the posterior  
 733 termination of the iliac crest (Figure 9). Second, if, after four treatments, the participant does not  
 734 respond (see Section B below for criteria of clinical response), the kidney-bladder distinct meridian  
 735 (module #4) will be activated for sessions 5-16. Distinct meridians are often needed to activate deep  
 736 meridian energy in treating refractory conditions. The kidney-bladder distinct meridian consists of  
 737 bilateral KI-10, BL-10, and BL-40 (which is activated in the principle treatment). Since BL-40 will be taken

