### Decision algorithms

Although minimal flexibility is permitted, there are still TWO specific times during the treatment period that the acupuncturist will make a decision regarding WHICH TREATMENT MODULES to activate for subsequent sessions (Figure 10). Modules #1 and #2 will be activated in ALL treatment sessions. On session 1, depending on whether or not the pain radiates to buttocks and hips, Module #3 may be activated. On session #5, we will assess if the participant has responded clinically to the first four treatments. A response is defined as either  $\geq 30\%$  reduction of original pain rating or  $> 2$  out of 10 points on the visual analog scale (VAS) of pain. If there is a response, the previous regimen will be continued. If not, we will activate Module #4 for the remainder of the treatment sessions (sessions 5 to 16).

[figure not shown]

**Figure 10. Decision algorithms within the VA protocol (made by acupuncturist).** Module 1 = modified PENS (local); Module 2 = KD-BL meridian tonification (distal); Module 3 = periosteal (local); Module 4 = distinct meridian (distal). In addition to these main treatment modules, standardized heat and auricular therapy are applied at the beginning of all verum sessions.

Finally, we do not expect the treatment algorithm above to unblind the participants in the verum arm because: A) At the initial evaluation with the acupuncturist, all participants will be informed that they will receive treatments which may or may not vary from time to time depending on their specific conditions; B) BOTH VA and PA participants will be filling out STANDARDIZED questionnaires assessing their treatment response as part of the trial data collection; C) The additional module (module 4) is based on TCM principles, and does NOT involve electrical stimulation NOR additional points in the back. As such, unless the patients are well-versed in TCM, these 3 additional points should NOT draw extra attention from the participants leading to unblinding; D) On the other hand, the PA patients will be subject to the same rigorous evaluations, rituals, except they won't have the extra mystery points. Again, unless the patient is well versed in TCM theory and practice, the chance of unblinding the PA folks should be also minimal.

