#### D. Order of tasks for each VA session

After the patient is placed in the prone position, the heat and auricular modules (minor) are activated, the placement of the body needles should then start. The goal is to allow the PENS module (and the periosteal module, if included) to be stimulated for 20-25 minutes and the principle meridian (KI 3 to KI-7) to be stimulated for 15 minutes. Furthermore, GV-20 should be placed first (immediately after auricular needles are placed) to help with sedation.

Therefore, the order of actions should be:

Prone positioning, heat application, placing auricular needles,

GV-20, PENS, periosteal, start e-stim for both PENS and periosteal,

Shaoying-Taiyang circuit +/- distinct meridian circuit (if included), finally start e-stim for KI-3 to KI-7.

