**B. Treatment flexibility**

The PA treatment should be identical for ALL participants assigned to the PA arm. There will be no treatment flexibility for PA. We are not concerned that lack of treatment flexibility might unblind the participant as acupuncturists in real life may use fixed points in multiple sessions after a thorough initial evaluation.

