1201 **Level 2:** The PI will report the event(s) to the DSMB.

1202 **Level 3:** The DSMB will decide, based on the severity and time course of the reported adverse, whether  
 1203 or not to terminate the participation of the participant and at the same time to break the blind. The  
 1204 information of treatment delivered and settings where the adverse event occurred would be important  
 1205 to minimize such events from happening again in the future.

1206 **6.2.4 Treatment Visits**

1207 Treatment Visits. Each participant will receive 12 treatment sessions. For each session, the participant  
 1208 fills out adverse event form at the beginning of the session (except for the first session), the  
 1209 acupuncturist fills out the treatment CRF near the end of the session. Sessions 1, 2, 5 and 12 will contain  
 1210 specific assessments, as outlined below.

1211 Treatment Session 1: 60 minutes

- 1212 • Acupuncturist will perform initial history and physical. History will include similar information as  
 1213 original baseline visit (pain location, duration, character, intensity, medication list, past medical  
 1214 and surgical history, previous allopathic and CAM treatment for back pain; as well as at TCM  
 1215 related question. Physical exam will include pulses, tongue exam according to TCM, as well as  
 1216 lumbar and low extremity palpation, range of motion, as well as anything else can be  
 1217 comfortably performed by the acupuncturist. These details will be recorded in the **Acupuncture**  
 1218 **Intake CRF**.
- 1219 • Most importantly, the acupuncturist will record a) if the participant experiences pain in  
 1220 hips/upper thighs; b) rating of back pain over the last 7 days using an 11-point (0-10) numerical  
 1221 rating scale (NRS).

- 1222 • Treatment will be administered per protocol (see Section 5.1)
- 1223 • Participant will complete **Stanford Expectancy of Treatment** BEFORE and AFTER the 1st
- 1224 treatment
- 1225 • Acupuncturist will complete session record on Visit Notes CRF
- 1226 • Acupuncturist will schedule/confirm next treatment session(s)
- 1227 Treatment sessions 2: 45 minutes
- 1228 • Participant will complete adverse event form before session starts.
- 1229 • Treatment will be administered per protocol (see Section 5.1)
- 1230 • Participant will complete **Vincent Credibility Scale** after the 2nd session.
- 1231 • Acupuncturist will complete session record on Visit Notes CRF

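### In the verum arm only, pain location decides whether Module 3 is added, so a widespread-pain-by-arm interaction can predict response to the verum regimen but cannot by itself support the mechanistic reading of Hypothesis 1

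*Protocol*

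**What the plan says.** **Treatment rule, verum.** Section 5.1.2.A switches on Module 3 by pain location: pain reaching the "buttocks and hips, we will activate module #3, the periosteal protocol for all session". The module consists of needling "and paired stimulation of the posterior superior iliac spine (PSIS) and a deep muscular point in the" affected gluteal region. The decision algorithm in 5.1.2.B puts the decision at the first visit: "On session 1, depending on whether or not the pain radiates to buttocks and hips, Module #3 may be activated". Section 5.1.2.D gives the dose of stimulation: "The goal is to allow the PENS module (and the periosteal module, if included) to be stimulated for 20-25 minutes".

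**Treatment rule, sham.** Section 5.1.3.B says "The PA treatment should be identical for ALL participants assigned to the PA arm" and "There will be no treatment flexibility for PA". Table 1 in 5.1.1 repeats the contrast: point selection is flexible in verum, partly by baseline anatomy, and not flexible in sham.

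**Predictor.** Hypothesis 1 (1.1, repeated in 9.1) expects "more wide-spread pain (WSP) (quantified by number of painful areas marked by the participant on a standardized body map" to go with greater pain reduction in verum than in sham, under the aim on ascending sensitization.

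**Analysis.** Section 9.6 sets out the analysis for temporal summation: correlation, regression by arm, and interaction with treatment group. It then applies the same analyses to widespread pain. The adjusters it names as examples are demographics and baseline pain level. It says that identified associations can help explain the mechanism of the treatment effect.

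**Recording.** At session 1 (6.2.4), "Most importantly, the acupuncturist will record a) if the participant experiences pain in" the hips or upper thighs. This step is not limited to one arm.

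**The concern.** The same baseline feature, where the pain is, enters the trial twice. It feeds the WSP count and, in one arm only, it sets how much treatment is given. A participant who marks more body areas is more likely to have pain in the buttocks and hips. In verum that participant gets an extra needled and electrically stimulated pair of points in every session. The comparable sham participant gets nothing extra.

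If Module 3 adds any pain relief, verum participants with high WSP will improve more, and the WSP slope will differ between arms in the direction that Hypothesis 1 predicts. The correlation of WSP with outcome within verum is affected in the same way. Section 5.1.2.B itself argues that a uniform treatment makes a common mechanism easier to identify, and Module 3 departs from uniformity along a predictor under test. The protocol considers whether its decision algorithm could unblind participants. It does not consider that the algorithm ties treatment content to WSP.

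What is at stake is the conclusion drawn: a finding about what was done to participants with hip and buttock pain could be reported as a finding about central pain processing.

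**Working it through.** **1. The passages side by side**

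| Element | Verum | Sham |
|---|---|---|
| Response to buttock and hip pain | Module 3 added, all sessions (5.1.2.A) | None (5.1.3.B) |
| Stimulation of that module | 20-25 minutes per session (5.1.2.D) | Not applicable |
| WSP count | Body-map areas | Body-map areas |
| Adjusters named as examples (9.6) | Demographics, baseline pain | Demographics, baseline pain |

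So the trigger is related to WSP in both arms, and to treatment content in verum alone.

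**2. The plan's own figures**

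Section 9.2 states 50 per arm and about 80% power for a correlation of 0.4. By Fisher's transformation, Φ(atanh(0.4)·√47 − 1.96) = 82.8%, which agrees with a rounded 80%. For the interaction it states 80% power for a difference of 0.5 between correlations, without giving the two correlations or the sidedness. Two-sided, 0.4 vs −0.1 gives 71.9%, 0.5 vs 0 gives 75.9% and 0.6 vs 0.1 gives 82.0%, so the 80% can be neither confirmed nor refuted. The present point does not depend on it.

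**3. Size of the induced correlation**

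The documents give no share of participants with the trigger (p), no correlation of trigger with WSP (ρ) and no Module 3 effect (d, in SD of outcome). All three are assumptions here. With no WSP effect of its own, the verum correlation is

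r = d·ρ·√(p(1−p)) / √(1 + d²·p(1−p)),

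and the sham correlation is zero.

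With p = 0.5, so √(p(1−p)) = 0.5:

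- d = 0.3, ρ = 0.4: 0.06 / √1.0225 = 0.06
- d = 0.8, ρ = 0.6: 0.24 / √1.16 = 0.22

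**4. Rejection rate of the nominal 5% interaction test**

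Simulation: 50 per arm, 4,000 trials per setting, p = 0.5, linear model with arm, WSP and arm × WSP.

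| Module 3 effect | Verum correlation (ρ = 0.4 / 0.6) | Rejection (ρ = 0.4 / 0.6) |
|---|---|---|
| 0.3 SD | 0.06 / 0.09 | 6.3% / 7.3% |
| 0.5 SD | 0.10 / 0.15 | 8.0% / 11.7% |
| 0.8 SD | 0.15 / 0.22 | 11.1% / 20.7% |

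A hand check by Fisher's transformation uses √(2/47) = 0.206. For r = 0.22, 0.227 / 0.206 = 1.10, and Φ(1.10 − 1.96) + Φ(−1.10 − 1.96) is about 20%. For r = 0.06, 0.059 / 0.206 = 0.29, which gives about 6%. Both agree with the table.

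A separate simulation over a wider grid (p 0.3 to 0.5, ρ 0.3 to 0.7, d 0.3 to 0.8; 3,000 trials per setting) gave rejection from about 5% to 26%. With d = 0 it stayed near 5%.

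**5. Effect and cost of adjustment**

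Adding trigger and trigger × arm brought rejection back to 4.7% to 5.4% in the settings of step 4, and to about 5% across the wider grid. The standard error of the WSP interaction rose by a factor of 1.07 to 1.26. The variance-inflation formula 1/√(1 − ρ²) gives a similar figure: 1.09 at ρ = 0.4 and 1.25 at ρ = 0.6.

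Applied to a nominal 80% power, with an unchanged effect:

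- factor 1.07: Φ(2.80/1.07 − 1.96) = Φ(0.66), about 74%
- factor 1.26: Φ(2.80/1.26 − 1.96) = Φ(0.26), about 60%

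**6. Trigger wording**

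Section 5.1.2.A makes activation mandatory, while the decision algorithm in 5.1.2.B makes it permissive. Both name buttocks and hips. The session 1 record in 6.2.4 names hips and upper thighs. The item collected therefore does not match the rule that it would have to represent.

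**The case against.** The strongest objection is that the trial sets out to predict response to acupuncture as delivered, and its title calls the approach pragmatic. Module 3 belongs to that regimen. If participants with more painful areas gain more from it than from sham, WSP does predict response to verum, and randomisation supports that comparison. This stands. A reader might infer that any such interaction would be a false positive, or that it would arise although WSP predicts nothing. The documents do not support that. In the simulated settings WSP really does correlate with verum outcome, through the treatment rule, and taking WSP into the Aim 3 prediction model is no error. Only the mechanistic reading is compromised.

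Second, the effect of Module 3 may be small. Section 5.1.2.B cites evidence that point choice may not matter as long as local and distal points are stimulated, and Modules 1 and 2 already do this for every verum participant. That is a fair reason to give the low end of the range weight. It does not settle the matter, because Module 3 adds a stimulated pair to those points and does not exchange one point for another.

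Third, the adjuster list in 9.6 is open, an SAP could add the trigger, and the protocol calls these aims exploratory and plans to verify findings in larger trials. All true, and this limits the seriousness. The link itself, however, lies in the treatment rule and would remain under any SAP.

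Fourth, adjustment has limits. By rule, no verum participant with the trigger goes without Module 3, so the model cannot separate radiation from Module 3. Hip and buttock pain may also be part of widespread pain, so conditioning on it may remove real signal. This is why the adjusted model should support the main test and not replace it.

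**Conclusion.** The point holds as a limit on interpretation. The protocol ties verum treatment content to a feature that overlaps with WSP, gives sham no counterpart, and names no adjuster that would separate the two. A WSP-by-arm interaction would validly predict response to the full verum algorithm. It would not, on its own, be evidence that ascending sensitization drives response.

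The structure is certain from the text; the size is not. With half of participants eligible, a trigger-WSP correlation of 0.4 to 0.6 and a Module 3 effect of 0.3 to 0.8 SD, all assumed, the nominal 5% test rejects in about 6% to 21% of trials when WSP has no effect of its own. At 0.3 SD the excess is one to two percentage points, which is negligible. If Module 3 adds nothing, there is no distortion. The mismatch in trigger wording is a separate, smaller defect that can be read directly from the text.

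**What to change.** - **Keep** the section 9.6 WSP-by-arm interaction as the analysis of prediction.
- **Add** one prespecified supporting analysis that includes trigger (yes/no) and trigger-by-arm next to WSP and WSP-by-arm. If the body map's regions allow (the protocol does not describe them), a WSP count that leaves out the low back, buttock and hip areas is an alternative. The schedule in 6.1 collects the body map at screening and at the pre-treatment visit, before randomisation. The alternative therefore does not rely on a session 1 record made by an acupuncturist who knows the arm.
- **State the reading in advance.** Give the mechanistic interpretation of Hypothesis 1 for WSP only if the estimate is consistent in the supporting analysis. Otherwise report the result as prediction of response to the full verum algorithm.
- **Reconcile** the trigger wording across 5.1.2.A, the decision algorithm in 5.1.2.B and the session 1 intake in 6.2.4, so that the item recorded in both arms matches the rule applied. Which wording governs is for the investigators to decide.

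**Cost:** one wording change on the intake form and two model terms, with no change in participant numbers. The supporting model is less precise (standard error about 7% to 26% wider, or roughly 74% to 60% power where the main test has 80%). Judge it by consistency of the estimate and not by significance. It cannot separate radiation from Module 3 itself, and the report should say so.

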## B. Treatment flexibility and decision algorithms

### Flexibility in VA

We will allow very little flexibility in the treatment for the proposed clinical trial because of three reasons. First, in contrast to many other clinical trials, our primary interest is in the mechanism of electroacupuncture (EA). As such, the more unified the treatment approach, the easier it will be to identify a common mechanism underlying electroacupuncture. Second, Helm's approach to EA allows very little variation because: 1) the modified PENS uses a standard protocol; 2) the protocol assumes most CHRONIC low back pain is due to a combination of blockage of Qi in the bladder meridian and vacuity in the Kidney organ, further limiting the TCM choice points. Third, previous studies have shown, at least in the case of low back pain, the choice of points may not matter as long as local and distal points from the bladder and kidney meridians are stimulated.

### Decision algorithms

Although minimal flexibility is permitted, there are still TWO specific times during the treatment period that the acupuncturist will make a decision regarding WHICH TREATMENT MODULES to activate for subsequent sessions (Figure 10). Modules #1 and #2 will be activated in ALL treatment sessions. On session 1, depending on whether or not the pain radiates to buttocks and hips, Module #3 may be activated. On session #5, we will assess if the participant has responded clinically to the first four treatments. A response is defined as either  $\geq 30\%$  reduction of original pain rating or  $> 2$  out of 10 points on the visual analog scale (VAS) of pain. If there is a response, the previous regimen will be continued. If not, we will activate Module #4 for the remainder of the treatment sessions (sessions 5 to 16).

[figure not shown]

**Figure 10. Decision algorithms within the VA protocol (made by acupuncturist).** Module 1 = modified PENS (local); Module 2 = KD-BL meridian tonification (distal); Module 3 = periosteal (local); Module 4 = distinct meridian (distal). In addition to these main treatment modules, standardized heat and auricular therapy are applied at the beginning of all verum sessions.

Finally, we do not expect the treatment algorithm above to unblind the participants in the verum arm because: A) At the initial evaluation with the acupuncturist, all participants will be informed that they will receive treatments which may or may not vary from time to time depending on their specific conditions; B) BOTH VA and PA participants will be filling out STANDARDIZED questionnaires assessing their treatment response as part of the trial data collection; C) The additional module (module 4) is based on TCM principles, and does NOT involve electrical stimulation NOR additional points in the back. As such, unless the patients are well-versed in TCM, these 3 additional points should NOT draw extra attention from the participants leading to unblinding; D) On the other hand, the PA patients will be subject to the same rigorous evaluations, rituals, except they won't have the extra mystery points. Again, unless the patient is well versed in TCM theory and practice, the chance of unblinding the PA folks should be also minimal.

